##### **Randomization:**

By centre using sealed envelopes 1:2 for BMS to DES and 1:1: for the DES subgroups.

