##### **Statistics:**

A sample size of 800 patients/stent type (753 plus compensation for a withdrawal rate of 5 to 6%) would provide a power of more than 90% to detect, at an alpha level of 0.05 in a two

tailed test, a significant difference between the BMS group and the DES group. This sample size will also allow to detect a significant difference between the BMS and each of the DES groups with a power of 80% at an alpha level of 0.027.

Intention to treat analysis: bivariable group comparisons will be first performed, then time to event will be evaluated both by Kaplan Meier statistics and Cox-regression analysis taking into account influential factors.

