## 9. Sample Size calculation

In the 558 patients of BASKET/BASKET-LATE with treatment of large native vessels, cardiac deaths and non-fatal MIs were seen in 6% of BMS compared to 11.2% of DES treated patients ( $p=0.05$ ) after a follow-up of 18 months. Based on a slightly more conservative assumption (i.e. 6.0 vs. 10.5% after follow-up of 24 months) and on the design of the proposed study, a total of 753 patients for the BMS group and a total of 1506 patients for the DES group (which includes the XienceV® and Nobori® groups) would have to be included to reject the null hypothesis that the event rates for the DES and BMS groups are equal at an alpha level=0.05 in a two-tailed test with probability of more than 90% (power). In view of an expected withdrawal rate of 5-6% and the 2:1 randomization, we plan to enroll 3x800 patients into the study or a total of 2400 patients; i.e. we could still detect a relative difference of 22% between BMS and DES at an alpha level of .027 with a power of 70% if the BMS rate stays the same, and with a slighter higher power an an alpha level of .05 if the BMS rate would be 5.5% instead of 6%. To address the second aim (comparison of BMS with each of the two DES) within BASKET-PROVE II, the sample size of 800 patients per stent group will allow to reject the null hypotheses that the event rates for each of the DES and the BMS are equal at an alpha level of 0.027 in a two-tailed test with a power of 80%. A simulation showed that a nominal alpha of 0.027 is appropriate to adjust for the duplicity of testing in the following setting: if three groups of equal size are compared with respect to the relative frequency of a certain outcome, the z-standardized differences ( $p_2-p_1$ ) and ( $p_3-p_1$ ) follow a 2-dimensional normal

distribution with variance 1 and covariance 0.5 under the null hypothesis. The Fisher's exact test will be used to evaluate the above hypotheses.

If we assume a total inclusion rate of 170 patients per month as in BASKET-PROVE by all participating centres, we should finish inclusion within 13-15 months. If results of BASKET-PROVE should differ markedly from these assumptions, i.e. difference in rates in cardiac death/MI of BMS patients vs. XienceV® patients <3.0% or >5.0%, then these sample size considerations will have to be reassessed.

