## **10. Data handling and Analyses**

Data management will be based on experience in other large multicenter trials (17,30). Thus, an internet-based electronic CRF will be used for data management. A secure website, accessible by password only, will be provided for data entry. Data will be stored centrally using an SQL-database. Quality of data will be assured by regular on-site monitoring visits, comparing data entered in CRFs with source documents. After monitoring, changes in CRF will be done electronically and only be possible by monitors and study coordination.

The following data will be recorded, in analogy to BASKET-PROVE I:

- Patient history and demographics
- CAD risk factors
- Comorbidities
- Indication for PCI
- Baseline angiographic and procedural characteristics
- Relevant data of stent use and concomitant drug use
- Serious adverse events during follow-up

- Events during follow-up (i.e. all hospitalisations, all coronary interventions, all bleeding, death)
- EQ-5D

For the statistical analysis, the data will be extracted from this database and transferred to and analysed in the commercially available statistical package SPSS v.15.0.

Bivariable comparisons of the DES group with the BMS group will be done using Fisher's exact test for proportions and the Mann-Whitney U-test, for continuous variables. P-values for the comparisons of each of the DES groups to the BMS group will be adjusted using the Bonferroni-Holm method if multiple comparisons of proportions or the Dunnett-Hsu if multiple comparisons of survival curves are performed. Time to event will be evaluated both by Kaplan Meier statistics and multivariable Cox-regression analysis taking into account further influential variables.

Historical comparisons of net clinical benefits will be only of descriptive character.

A priori, missing values will not be imputed. Losses to follow-up will be incorporated since survival analysis will be performed. If outliers values are observed, each will be examined. If it is thought that their cause is of clinical nature, they would be kept in the analysis, otherwise they will be set to missing.

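### The test named for the primary and pairwise hypotheses (Fisher's exact test) cannot use censored follow-up, although the protocol relies on survival analysis to handle losses

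*Protocol*

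**What the plan says.** Protocol Section 9 sets out the null hypotheses of equal event rates for DES against BMS (two-sided alpha 0.05) and for each DES against BMS (alpha 0.027). It closes by stating that Fisher's "exact test will be used to evaluate the above hypotheses". It plans 753 BMS and 1506 DES patients, raised to 3 x 800 for an expected withdrawal of 5-6%.

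Section 10 repeats Fisher's test for proportions and then states: "A priori, missing values will not be imputed. Losses to follow-up will be incorporated since survival analysis will be performed".

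The synopsis (Statistics) declares an intention-to-treat analysis in which "bivariable group comparisons will be first performed, then time to event will be evaluated both by Kaplan Meier statistics and Cox-regression analysis". Sections 8 and 9 therefore treat the endpoint as a 24-month proportion, while the only sentence on losses refers to an analysis that comes second.

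**The concern.** Fisher's test needs a yes/no status at 24 months for each patient in the table. A patient who leaves event-free at, say, month 8 has no such status. A survival analysis would use the 8 months; a 2x2 table cannot. With imputation excluded, two codings remain:

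- leave the patient out, which is not intention to treat;
- count the patient as event-free, which assumes what was not observed.

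The protocol's statement on losses supports neither coding, because it applies only to the Kaplan-Meier and Cox analyses. The expected loss (5-6%) is about as large as the assumed BMS event rate (6.0%). The trial is open-label, and Section 5 schedules no follow-up questionnaire before 24 months, so losses could differ between arms. At stake is a primary verdict that depends on a coding decision which the protocol's own sentence appears to settle but does not.

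**Working it through.** **Inputs from the protocol (Section 9).** Event rates 6.0% (BMS) and 10.5% (DES); 753 and 1506 patients, enrolled as 800 and 1600; withdrawal 5-6%, which is 120 to 144 of 2400. **Assumed, not in the protocol:** how losses split between arms, when they occur, and the event risk of lost patients.

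**1. The plan's own figures.** Pooled rate = (753 x 0.06 + 1506 x 0.105)/2259 = 0.090. The standard error is 0.01277 under the null and 0.01172 under the alternative. Power = Phi[(0.045 - 1.96 x 0.01277)/0.01172] = 95.6%. Exact enumeration of Fisher's test gives 95.4%. Each DES against BMS at alpha 0.027 with 753 per group gives 83.3% (normal) or 81.5% (exact Fisher). Both stated powers, more than 90% and 80%, are reproduced. Also 753/0.95 = 793 and 753/0.94 = 802, which matches 800.

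**2. Equal losses.** Assume 5.5% lost in each arm, uniformly over 24 months, with constant hazards. If a lost patient's later events go unseen, the expected crude rate is (1 - L) x p + L x q, where q is the mean risk up to the time of loss (3.03% for BMS, 5.35% for DES):

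- BMS: 0.945 x 6.0% + 0.055 x 3.03% = 5.84%
- DES: 0.945 x 10.5% + 0.055 x 5.35% = 10.22%

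The difference is 4.38 points instead of 4.50, and exact Fisher power with 800/1600 is 96.0% against 96.4% without loss. In simulation (2000 runs per setting, Monte Carlo error about 0.5 points), power was 95.0-95.3% for Fisher and 95.3-95.5% for the log-rank test.

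**3. Unequal losses, one data set, two codings.** Assume 48 BMS and 130 DES events, with 4% of BMS (32) and 7% of DES patients (112) lost without a recorded event. That is 144/2400 = 6.0% overall, within the protocol's expectation.

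| Coding of lost patients | BMS | DES | Fisher p |
|---|---|---|---|
| Event-free | 48/800 = 6.00% | 130/1600 = 8.13% | 0.069 |
| Dropped | 48/768 = 6.25% | 130/1488 = 8.74% | 0.039 |

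With 48 BMS events the verdict differs for 129 to 131 DES events. With losses reversed (7% BMS, 4% DES) it differs the other way: at 134 DES events p is 0.041 (event-free) or 0.070 (dropped). With 6% lost in both arms and 48 BMS events, the two codings never disagreed.

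**4. Power under unequal losses (simulated, lost counted as event-free).**

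| Assumed loss, BMS / DES | Fisher | Log-rank |
|---|---|---|
| 3% / 7% | 95.0% | 96.2% |
| 2% / 9% | 93.0% | 96.5% |

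The 2%/9% case is (16 + 144)/2400 = 6.7% overall, slightly beyond the protocol's range. There, exact Fisher type I error at a common 9% rate is 5.4%.

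**5. What a survival method does not cure.** Suppose 6% are lost in each arm and lost patients have twice the event risk. Rates among those followed are p/(0.94 + 0.06 x 2) = p/1.06: 5.66% and 9.91%, a difference of 4.25 points. If the losses come soon after the procedure, censored patients contribute almost no follow-up and Kaplan-Meier gives the same 4.25 points. With losses spread over 24 months a simulation gave 4.39, still short of 4.50.

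**The case against.** The best defence is that Fisher's test suits the endpoint as defined: freedom from cardiac death or MI after 24 months is a fixed-time proportion, the hypotheses concern event rates, and endpoint adjudication is blinded to stent type. How a lost patient enters the 2x2 table is often left to a statistical analysis plan, which is not at hand. That defence would succeed if the protocol were silent on losses. It is not: Section 10 gives survival analysis as the reason why losses are covered, and the test in Section 9 is not one.

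Four stronger readings are tempting, and the documents do not support them.

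- **That no test is named as decisive.** Section 9 does name one. Section 10 is loose in giving separate multiplicity adjustments for proportions and for survival curves, but Kaplan-Meier and Cox are placed second.
- **That the power or sample size is wrong on this account.** The stated powers for the primary and pairwise comparisons are reproduced, and equal losses barely change the primary power.
- **That the test is invalid because it ignores centre.** "By centre using sealed envelopes" may only describe where allocation takes place; no stratified scheme is stated. Even under stratification the unstratified Fisher test remains valid. Ignoring centre cost up to about 2 points of power in the settings simulated.
- **That a log-rank test removes bias from lost patients being at higher risk.** It assumes non-informative censoring, as step 5 shows.

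**Conclusion.** The inconsistency is real: the stated handling of losses does not apply to the test that decides the primary and pairwise hypotheses. Its practical size is modest. Under equal loss it costs less than 1 point of power at 6.0% against 10.5%. It becomes material when losses differ between arms and the result is near the threshold, where two codings that the text permits gave p = 0.039 and p = 0.069. That example rests on an assumed 4%/7% split and a narrow band of event counts; the documents give no losses by arm. This should be fixed before outcome data are seen, but it is not a defect that stops the trial.

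**What to change.** In Section 9, replace Fisher's test for the primary and both pairwise comparisons by an intention-to-treat analysis of time to first cardiac death or non-fatal MI, censored at 24 months or last contact, using a log-rank test or a Cox model with stent group only; name one. Report the Kaplan-Meier 24-month risk difference with 95% confidence interval. State the one multiplicity rule that goes with the pairwise tests.

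Keep Fisher's test, with a written rule for patients lost before 24 months, and the covariate-adjusted Cox model as supportive analyses. Add a sensitivity analysis that varies the assumed event risk of lost patients separately by arm. Stratifying by centre is optional.

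The cost is wording. Event dates are already needed for the planned Kaplan-Meier and Cox analyses. The sample size stays, and simulated log-rank power at the planned rates is about 95% with 5.5% loss in each arm.

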## **10. Data handling and Analyses**

Data management will be based on experience in other large multicenter trials (17,30). Thus, an internet-based electronic CRF will be used for data management. A secure website, accessible by password only, will be provided for data entry. Data will be stored centrally using an SQL-database. Quality of data will be assured by regular on-site monitoring visits, comparing data entered in CRFs with source documents. After monitoring, changes in CRF will be done electronically and only be possible by monitors and study coordination.

The following data will be recorded, in analogy to BASKET-PROVE I:

- Patient history and demographics
- CAD risk factors
- Comorbidities
- Indication for PCI
- Baseline angiographic and procedural characteristics
- Relevant data of stent use and concomitant drug use
- Serious adverse events during follow-up

- Events during follow-up (i.e. all hospitalisations, all coronary interventions, all bleeding, death)
- EQ-5D

For the statistical analysis, the data will be extracted from this database and transferred to and analysed in the commercially available statistical package SPSS v.15.0.

Bivariable comparisons of the DES group with the BMS group will be done using Fisher's exact test for proportions and the Mann-Whitney U-test, for continuous variables. P-values for the comparisons of each of the DES groups to the BMS group will be adjusted using the Bonferroni-Holm method if multiple comparisons of proportions or the Dunnett-Hsu if multiple comparisons of survival curves are performed. Time to event will be evaluated both by Kaplan Meier statistics and multivariable Cox-regression analysis taking into account further influential variables.

Historical comparisons of net clinical benefits will be only of descriptive character.

A priori, missing values will not be imputed. Losses to follow-up will be incorporated since survival analysis will be performed. If outliers values are observed, each will be examined. If it is thought that their cause is of clinical nature, they would be kept in the analysis, otherwise they will be set to missing.

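### Each DES versus BMS: section 9 fixes a single-step alpha of 0.027 and section 10 fixes Bonferroni-Holm for the same Fisher comparisons, and the protocol does not say which decides

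*Protocol*

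**What the plan says.** Comparing each DES with the BMS is secondary aim B (section 2).

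- **Section 9** gives the multiplicity rule as a fixed level per comparison: "A simulation showed that a nominal alpha of 0.027 is appropriate to adjust for the duplicity of testing in the following setting". The setting is three equal groups whose two standardized differences from BMS share a "distribution with variance 1 and covariance 0.5 under the null hypothesis". It claims 80% power for each pair at that two-sided level, and adds: "The Fisher's exact test will be used to evaluate the above hypotheses".
- **The synopsis** (Statistics) repeats the level for BMS against each DES: "with a power of 80% at an alpha level of 0.027".
- **Section 10** says "P-values for the comparisons of each of the DES groups to the BMS group will be adjusted using the Bonferroni-Holm method" and limits the scope: "if multiple comparisons of proportions or the Dunnett-Hsu if multiple comparisons of survival curves are performed". It names Fisher's exact test for proportions but gives no family-wise level.

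The protocol nowhere says that 0.027 is for planning only, or that one section overrides the other.

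**The concern.** Fisher's exact test compares proportions, so the section 9 level and the section 10 adjustment apply to the same two p-values. They are different procedures:

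- **Section 9, single-step:** each DES differs from BMS if its own p is at most 0.027, whatever the other p is.
- **Section 10, Holm at 0.05:** the smaller p must be at most 0.025; only then is the larger p compared with 0.05.

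What is at stake is the significance statement on an individual stent. Section 15 says that differences between stent types will help to define the safest and most effective one. If the rule is still open when results are seen, it can be chosen to suit them. A third possibility, comparing Holm-adjusted p-values with 0.027, would adjust twice.

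**Working it through.** **Inputs.** From section 9: event rates 6.0% (BMS) and 10.5% (DES); 753 per stent group before the withdrawal allowance (1506 DES = 2 × 753); 800 per group enrolled; two-sided 0.027; Fisher's exact test. Assumed: family-wise 0.05 for Holm. Also assumed, as a second scenario: 9% in both DES groups, since a difference of 9 − 6 = 3 points is the smallest that section 9 accepts from the predecessor trial without reassessing the sample size.

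**1. The plan's 0.027.** Solve P(|Z1| > c or |Z2| > c) = 0.05 for a bivariate normal with correlation 0.5. This gives c = 2.212, a nominal level of 0.02696. At 0.027 the family-wise error is 0.0501. The figure is right.

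**2. The plan's 80%.** n = [z(α/2)·√(2p̄q̄) + z(β)·√(p1q1 + p2q2)]² / Δ², with p̄ = 0.0825, Δ = 0.045, z(α/2) = 2.2115 and z(β) = 0.8416:

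n = [2.2115 × 0.3891 + 0.8416 × 0.3878]² / 0.002025 ≈ 696 per group.

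With continuity correction it is 740, close to 753. The power of Fisher's test itself at 753 per group is 81.5%. The 80% reproduces.

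**3. Where the rules disagree.**

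- Smaller p ≤ 0.025 and larger p above 0.027 but at most 0.05: Holm declares both DES different, section 9 only one.
- Smaller p above 0.025 but at most 0.027: section 9 declares at least one DES different, Holm none.

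Both occur with attainable counts at 753 per arm:

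- Events 45 (BMS), 80 and 67 (DES): p = 0.0014 and 0.0388. The second DES is significant under Holm (adjusted p 0.0388), not at 0.027.
- Events 46 (BMS) and 70 (one DES), the other DES with a larger p: p = 0.0259. Significant at 0.027, not under Holm (adjusted p 2 × 0.02586 = 0.0517).

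**4. How often.** Fisher's test, 753 per arm, probabilities summed over all possible event counts. A separate simulation of 100,000 trials per scenario agrees to within about 0.2 percentage points.

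| True rates BMS/DES/DES (%) | Any disagreement | Holm only | 0.027 only |
|---|---|---|---|
| 6/6/6 | 0.6% | 0.3% | 0.3% |
| 6/10.5/10.5 | 8.3% | 7.8% | 0.5% |
| 6/9/9 | 9.6% | 8.5% | 1.1% |
| 6/6/10.5 | 2.1% | 1.4% | 0.8% |

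At 800 per arm the 6/10.5/10.5 figure is 7.9%.

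**5. Power and error by rule**, 753 per arm. Power is at 6/10.5/10.5; the last row is at 6/6/6.

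| | Single-step 0.027 | Holm | Step-down Dunnett |
|---|---|---|---|
| A given DES | 81.5% | 85.1% | 85.4% |
| Both DES | 70.6% | 78.4% | 78.5% |
| At least one DES | 92.4% | 91.9% | 92.4% |
| Any false rejection under the null | 3.9% | 3.6% | 3.9% |

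If only one DES truly differs (6/6/10.5), power for that stent is 81.5% at 0.027 and 80.8% under Holm. The null figures lie below 0.05 because Fisher's test is conservative.

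**The case against.** The best defence is that 0.027 is a planning level. It stands under the sample-size heading, inside power statements, while section 10 is the analysis section and says how p-values will be handled. Planning on a fixed level and analysing with a step-down method is common practice. This reading is possible, but the text does not settle it: section 9 presents 0.027 as the correction for testing twice, derives it from a joint null distribution and names the test to be used.

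Four stronger readings might be inferred, and the documents do not support them:

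- **The 80% power is lost because section 10 uses another rule.** It is not. Power per DES is at least 80% under both rules and mostly higher under Holm. Only the chance of showing at least one DES different falls, by about half a point.
- **Type I error is inflated.** Each rule alone holds it at about 0.05. Inflation would need the rule to be picked after seeing the data.
- **The choice can turn a harmful stent into a safe one.** No rule changes the direction of an effect. A borderline p-value crosses a threshold or misses it, and nearly always the first DES is already significant.
- **Dunnett-Hsu is a third conflicting rule.** Section 10 confines it to survival curves, which is a different analysis.

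**Conclusion.** The inconsistency is real and modest. Two non-equivalent rules are fixed for the same Fisher comparisons, and the protocol does not say which decides. Under the planning rates the verdict on at least one stent depends on that choice in about 8% of trials, and in about 10% at 6/9/9%. In most of these Holm adds the second DES, whose p lies between 0.027 and 0.05. The opposite case, with the smaller p between 0.025 and 0.027, has a probability of about 0.5% and 1.1% in these two scenarios.

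The comparison is a secondary aim, and the primary pooled DES versus BMS test at 0.05 is untouched. The sizes assume Holm at family-wise 0.05, 753 evaluable patients per arm, Fisher's test and the event rates shown. The inconsistency itself does not depend on those rates. It is worth correcting because the correction costs almost nothing and settles in advance what may be concluded about each stent.

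**What to change.** State one rule for the Fisher comparisons of each DES with BMS, in the same words in the synopsis and in sections 9 and 10, with its family-wise level. Do so before any endpoint data are compared by stent group; the trial is open-label (section 4), so there is no formal unblinding step to rely on.

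- **Step-down Dunnett:** compare the smaller p with 0.027; if it is significant, compare the larger p with 0.05. Every rejection by either written rule is also a rejection here, so no power is lost. Its gain over Holm is small (0.2 to 0.5 points at the planning rates), so this is a convenience and not a necessity.
- **Either written rule, used throughout,** resolves the point equally well. With single-step 0.027 the power sentence stands. With Holm, restate the power for that rule and give its level.

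Whichever is chosen, do not compare Holm-adjusted p-values with 0.027, and keep the Dunnett-Hsu provision for survival curves. The cost is a few sentences of wording, with no extra patients.

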## 8. End-point definitions

1°end-point = freedom of combination of

- cardiac death (all death not clearly of extra cardiac origin)
- documented non-fatal MI (according to the current ESC-guidelines (28))

after 24 months.

2°end-points =

- non-MI related TVR
- major adverse cardiac events (MACE) = 1°end-point events + non-MI related TVR
- 1° end-point events up to 18 months (for comparison with BASKET and BASKET-LATE)
- stent thrombosis according to the ARC-definitions (29)
- components of the 1°end-points
- non-cardiac death, total death
- major non-CABG bleeding (need for surgery, blood transfusions, cerebral haemorrhages) during dual antiplatelet therapy (up to twelve months) – “net clinical benefit” = 1°end-point + bleeding.
- long-term follow-up after 36 and 60 months
- subgroups with
  - diabetes
  - acute coronary syndrome
  - ST-elevation MI
  - need for GP IIb/IIIa inhibitors
  - lesions >25 mm

End-points will be adjudicated by an independent Critical Events Committee (CEC) blinded to the stent type used.

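### Kaplan-Meier is named for every time-to-event analysis, but most of the cardiac endpoints leave out some or all deaths, so 1 − KM overstates their cumulative incidence, mainly at 36 and 60 months (minor)

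*Protocol*

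**What the plan says.** Section 10 sets the time-to-event methods in one general sentence: "Time to event will be evaluated both by Kaplan Meier statistics and multivariable Cox-regression analysis taking into account further influential variables". It also foresees a multiplicity adjustment for comparing several survival curves. On incomplete observation it says only: "Losses to follow-up will be incorporated since survival analysis will be performed". Deaths that fall outside an endpoint are not mentioned.

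Section 8 defines the endpoints. The fatal part of the primary composite is "cardiac death (all death not clearly of extra cardiac origin", so a clearly extracardiac death is not an event. The secondary endpoints include "non-MI related TVR", "major adverse cardiac events (MACE) = 1°end-point events + non-MI related TVR", the components of the primary endpoint, and "non-cardiac death, total death". They also include "long-term follow-up after 36 and 60 months".

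For the main hypotheses (BMS against DES, and each DES against BMS) section 9 states: "The Fisher's exact test will be used to evaluate the above hypotheses".

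**The concern.** Kaplan-Meier has one way to handle a patient who leaves the risk set without the event: censoring. For a patient lost to follow-up this is reasonable, because the event could still occur unseen. A patient who has died cannot later have an MI or a revascularisation. Censoring that death estimates the event rate in a hypothetical population where such deaths do not happen, and the result is always at least as high as the proportion of patients who actually have the event.

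The affected endpoints are:
- primary composite, cardiac death and MACE: non-cardiac death competes;
- non-fatal MI and non-MI related TVR: any death competes.

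At stake are the printed absolute rates and curves, above all at 36 and 60 months, where deaths have accumulated. They would also sit uneasily beside the crude proportions in the Fisher tests, which count a patient who died of another cause as event-free.

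A second question is whether the distortion could differ by arm. Under section 6, elective patients receive prasugrel for 1 month after BMS and 12 months after DES, while ACS patients receive 12 months in both arms. A difference in fatal bleeding between arms is therefore conceivable.

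**Working it through.** **1. The plan's own power figures.** Inputs from section 9: 6.0% against 10.5% at 24 months, 753 BMS and 1506 DES patients, two-sided alpha 0.05.
- Pooled rate = (753 × 0.06 + 1506 × 0.105) / 2259 = 0.090.
- SE under the null = √[0.09 × 0.91 × (1/753 + 1/1506)] = 0.01277.
- SE under the alternative = √[0.06 × 0.94/753 + 0.105 × 0.895/1506] = 0.01172.
- Power = Φ[(0.045 − 1.96 × 0.01277) / 0.01172] = Φ(1.70) = 95.6%. Simulation with Fisher's exact test gives 95.4%.

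For each DES against BMS at alpha 0.027 with 753 per group, simulated Fisher power is 81.4%. Both stated figures (more than 90%, and 80%) are confirmed. Neither uses Kaplan-Meier, so neither changes if the estimator is replaced.

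**2. Model for the size of the bias.** Constant yearly hazards: λ for the event, μ for competing death.
- True cumulative incidence: CIF(t) = λ/(λ+μ) × [1 − exp(−(λ+μ)t)].
- What Kaplan-Meier shows: 1 − exp(−λt).
- μ = −ln(1 − yearly death proportion), and λ is solved so that CIF(24 months) equals the chosen rate.

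The 6.0% and 10.5% come from section 9. The death rates, the TVR rates and the constant hazards beyond 24 months are assumptions.

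**3. One case in full.** DES, 10.5% at 24 months, non-cardiac death 2% per year: μ = 0.0202, λ = 0.0566.
- 24 months: CIF 10.50%, 1 − KM 10.71%, excess 0.21 points.
- 60 months: CIF 23.51%, 1 − KM 24.66%, excess 1.15 points.

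**4. Range of excess, in percentage points.**

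| Endpoint and assumed competing death | 24 months | 36 months | 60 months |
|---|---|---|---|
| Primary composite, BMS 6.0%; non-cardiac 0.5–2%/year | 0.03–0.12 | 0.07–0.26 | 0.17–0.70 |
| Primary composite, DES 10.5%; non-cardiac 0.5–2%/year | 0.05–0.21 | 0.11–0.45 | 0.29–1.15 |
| TVR, assumed 5–10% at 24 months; all-cause 1–4%/year | 0.05–0.41 | 0.11–0.87 | 0.29–2.19 |

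**5. Effect on the DES − BMS difference in the primary composite.**
- Non-cardiac death 1% per year in both arms: 4.54 instead of 4.50 points at 24 months, and 9.97 instead of 9.74 at 60 months.
- 0.5% BMS, 2% DES: 4.68 instead of 4.50 at 24 months, and 10.26 instead of 9.29 at 60 months (+0.97).
- 2% BMS, 0.5% DES: 4.43 instead of 4.50 at 24 months, and 9.72 instead of 10.13 at 60 months (−0.41).

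The standard error of the 24-month difference is about 1.2 points (step 1), so the shift at 24 months is well inside sampling error even with a fourfold imbalance in competing deaths.

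**The case against.** The strongest reply is that nothing here is misstated. Section 10 names two standard methods in a general sentence. It does not say that other-cause deaths are censored or that 1 − KM will be printed as absolute risk, and competing-risk handling is often left to an SAP, which is not shown. In part this stands: the censoring follows from applying the named method to the defined endpoints, and an SAP could refine it. But the protocol does name the estimator and foresees comparing survival curves, so the mismatch with its own definitions is worth correcting.

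Several stronger readings are tempting, and the documents do not support them:
- *All time-to-event endpoints are affected.* They are not. Total death has no competing event.
- *The main comparison is at risk.* It is not. It rests on Fisher's exact test, and a Cox hazard ratio remains valid for the cause-specific hazard.
- *Censoring differs by arm.* The difference in prasugrel duration makes this possible in elective patients only, and no figure in the protocol shows that it happens.
- *Bleeding and stent thrombosis belong on the list.* Bleeding is counted for at most twelve months and is not limited to non-fatal bleeds. Stent thrombosis is defined only by citation, so its treatment of death cannot be checked here.

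It is also fair to say that disagreement with the crude proportions is not unique to Kaplan-Meier. With the 5–6% withdrawal expected in section 9, Aalen-Johansen can differ from a crude proportion too; the two coincide only with complete follow-up. Finally, the larger late figures depend on assumed rates, and this population is described as being at low risk of restenosis.

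**Conclusion.** The point holds as a minor improvement to the choice of estimator. The direction of the bias is certain wherever non-endpoint deaths are censored; its size depends on mortality and TVR rates that the protocol does not give. For the 24-month primary rate it can be ignored. It becomes visible in the long-term results: up to about 1.2 points for the composite and 2.2 points for TVR at 60 months, at the top of the assumed ranges and with constant hazards. It does not threaten the confirmatory conclusion.

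**What to change.** Amend the time-to-event sentence in section 10 as follows:
- For the primary composite, cardiac death, non-fatal MI, non-MI related TVR and MACE, estimate cumulative incidence by Aalen-Johansen, with deaths outside the endpoint as competing events. The priority is TVR and the 36- and 60-month results.
- Keep Kaplan-Meier for total death.
- Keep Cox regression, described as a cause-specific hazard model.
- Show the incidence of competing deaths by arm beside each analysis, so that any imbalance can be seen.

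No new data are needed: non-cardiac and total death are already endpoints, and section 8 provides for blinded adjudication. The costs are slightly lower reported rates, one more table, and possibly software beyond the SPSS v.15.0 named in section 10; whether that version provides the estimator should be checked. Sample size, Fisher tests and multiplicity level stay as they are.
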